**Figure 1 Flow diagram for this trial**

**Interventions**

Patients in both groups will receive the same ERAS program except for the different interventions. For the control group, patients will be treated with endotracheal intubation for ventilation after anesthesia induction, a preoperative TAP block with 40 ml normal saline as control and local wound infiltration with 40 ml solution of ropivacaine 3 mg/kg plus dexamethasone 0.1 mg/kg at the conclusion of surgery. On the contrary, patients in the TAP+LMA group will have an LMA inserted for ventilation after induction, have a TAP block with 40ml solution of ropivacaine 3 mg/kg plus dexamethasone 0.1 mg/kg, and receive local wound infiltration with 40 ml normal saline at the conclusion of surgery. Guided by ultrasound, a subcostal TAP block will be performed bilaterally at the parasternal line and at the anterior axillary line, with 10ml solution injected in each site (**Figure 2**).

[figure not shown]

[figure not shown]

[figure not shown]

[figure not shown]

[figure not shown]

[figure not shown]

[figure not shown]

[figure not shown]

**Figure 2 Procedures of LMA ventilation and subcostal TAP block**

1. Double-tube LMA: ventral side; B. Double-tube LMA: back side; C. Placement of LMA; D.LMA ventilation and esophageal drainage; E.LMA positioning by fiberoptic bronchoscopy; F. positions of ultrasound probe for TAP block; G. Ultrasound image of TAP block: inner site; H. Ultrasound image of TAP block: lateral site.

(AT: airway tube, DT: esophageal drainage tube, M: mask, IL: inflation line, ST: stomach tube, G: glottal, VC: vocal cord, ①: parasternal line, ②: anterior axillary line, ③: xiphoid, ④: costal arch, white rectangle: ultrasound probe, IS: inner site, LS: lateral site, N: needle, LA: local anesthetic, RA: rectus abdominis, TA: transversus abdominis, EO: obliquus externus abdominis, IO: obliquus internus abdominis)

**Anesthesia and analgesia**

While in the operating room, all enrolled patients will be continuously monitored for standard measures including electrocardiogram, heart rate, non-invasive arterial blood pressure and oxygen saturation. Monitoring of Narcotrend Index (NI) is used for assessing patients’ depth of consciousness. Placement of a peripheral vein catheter is established for infusion. Radial artery catheterization is performed to monitor invasive arterial pressure and to measure blood gas.

After induction of total intravenous anesthesia with propofol/sufentanil/cis-atracurium, positive pressure ventilation will be performed in the patients of control group by ETI and in the patients of TAP+LMA group by LMA. Auscultation of respiratory tone, observation of respiratory parameters and examination with a flexible fiberoptic bronchoscopy is used to determine whether the laryngeal mask is in correct position. If necessary, gastric tubes will be placed with the help of a laryngoscope in the patients of control group or through the esophageal drainage tube of the LMA in the patients of the TAP+LMA group. Then, the procedures of ultrasound-guided subcostal TAP block will be implemented as described above.

Maintenance of anesthesia is achieved by administration of sevoflurane, remifentanil and cis-atracurium. Dosages of anesthetic drugs is adjusted to maintain arterial blood pressure and heart rate fluctuating in the range of -20% to +20% of the base value and NI fluctuating in the range of 37 to 56. If necessary, cardiovascular active drugs (i.e. norepinephrine, atropine, esmolol, nicardipine) will be used to maintain stable hemodynamics. Controlled-low Central Venous Pressure (CVP) technology is adopted to maintain CVP between 0 and 5 cmH_2_O during hepatectomy. This is done by restriction of fluid, control of anesthesia depth and stress response, adjustment of patients’ position, and application of vasoactive drugs (nitroglycerin and dobutamine). The CVP value will be restored to normal after completing the hepatectomy. Allogeneic blood transfusion will be administered if hemoglobin was less than 70 g/L. Body temperature is continuously monitored and maintained within 36～37℃ by multiple approaches including warmed infusion, application of electric blanket and preheated peritoneal irrigation.

At the conclusion of surgery, tropisetron 10mg is administered to prevent postoperative nausea and vomiting and sufentanil 0.1ug/kg is administered to alleviate remifentanil-induced hyperalgesia. Local wound infiltration is performed with different solution in the two groups, as described above. Multimodal analgesia is used postoperatively in both groups, including regional block, patient-controlled intravenous analgesia (PCIA) with sufentanil, intravenous parecoxib 40 mg twice per day for 3 days and oral analgesic.

**Study end-points**

The primary end-point of the study is postoperative time of readiness for hospital discharge. The discharge criteria include: pain score less than 4, solid diet without infusion, normal bowel movement, well-healed wound, normal organ function, normal count of white blood cell (WBC), no fever, life independence.

The secondary end-points are postoperative analgesic requirement within 48 hr, time to first flatus and overall medical cost. Blood glucose and lactate will be tested before anesthesia (t0), at surgical exploration (t1), at the conclusion of surgery (t2) and at departure from the post-anesthesia care unit (PACU) (t3). Dosages of anesthetics and vasoactive drugs, surgery duration, anesthesia duration, hepatectomy duration, duration of hepatic blood flow occlusion, bleeding volume, infusion volume and urine volume are recorded.

The postoperative pain intensity of the surgical site is assessed with the numerical rating scale (NRS), in which 0 represented no pain and 10 represented the most severe pain. Postoperative variables such as time to removing ETT or LMA, duration of PACU stay, time to first mobilization off the bed, incidence of nausea/vomiting within 48 hr and complications are also recorded and compared. The 40-item quality of recovery (QoR-40) survey is performed before surgery, at 1 and 3 days after surgery, and on the day of discharge, referred to other studies^[12, 13]^ and described as **the following figure**.

| **QoR-40 Questionnaire** | | | | | | | | |
| --- | --- | --- | --- | --- | --- | --- | --- | --- |
| Date:____/____/____ | Preoperative:_______ | | | Postoperative:______ | | | Study #:______ | |
| **PART A** | | | | | | | | |
| ***How have you been feeling in the last 24 hours?*** | | | | | | | | |
| (1 to 5, where: 1 = none of the time [poor], 2 = sometimes, 3 = often, 4 = most of the time, 5 = all of the time [excellent]) | | | | | | | | |
|  | | none of  the time | sometimes | | often | most of  the time | | all of the time |
| 1.Able to breathe easy | | 1 | 2 | | 3 | 4 | | 5 |
| 2.Being able to enjoy food | | 1 | 2 | | 3 | 4 | | 5 |
| 3.Have a good sleep | | 1 | 2 | | 3 | 4 | | 5 |
| 4.Feeling rested | | 1 | 2 | | 3 | 4 | | 5 |
| 5.Feeling comfortable | | 1 | 2 | | 3 | 4 | | 5 |
| 6.Having a general feeling  of well-being | | 1 | 2 | | 3 | 4 | | 5 |
| 7.Feeling in control | | 1 | 2 | | 3 | 4 | | 5 |
| 8.Able to write | | 1 | 2 | | 3 | 4 | | 5 |
| 9.Have normal speech | | 1 | 2 | | 3 | 4 | | 5 |
| 10.Able to wash, brush teeth orshave | | 1 | 2 | | 3 | 4 | | 5 |
| 11.Able to look after own appearance | | 1 | 2 | | 3 | 4 | | 5 |
| 12.Able to return to work or usual home activities | | 1 | 2 | | 3 | 4 | | 5 |
| 13.Able to communicate with hospital staff (when in hospital) | | 1 | 2 | | 3 | 4 | | 5 |
| 14.Able to communicate with family or friends | | 1 | 2 | | 3 | 4 | | 5 |
| 15.Getting support from doctors (when in hospital) | | 1 | 2 | | 3 | 4 | | 5 |
| 16. Getting support from nurses (when in hospital) | | 1 | 2 | | 3 | 4 | | 5 |
| 17. Having support from family or friends | | 1 | 2 | | 3 | 4 | | 5 |
| 18.Able to understand instructions or advice | | 1 | 2 | | 3 | 4 | | 5 |
| **PART B** | | | | | | | | |
| ***Have you had any of the following in the last 24 hours?*** | | | | | | | | |
| (5 to 1, where: 5 = none of the time [poor], 4 = sometimes, 3 = often, 2 = most of the time, 1 = all of the time [excellent]) | | | | | | | | |
|  | | none of  the time | sometimes | | often | most of  the time | | all of the time |
| 19.Moderate pain | | 5 | 4 | | 3 | 2 | | 1 |
| 20.Severe pain | | 5 | 4 | | 3 | 2 | | 1 |
| 21.Headache | | 5 | 4 | | 3 | 2 | | 1 |
| 22.Muscle pain | | 5 | 4 | | 3 | 2 | | 1 |
| 23.Backache | | 5 | 4 | | 3 | 2 | | 1 |
| 24.Sore throat | | 5 | 4 | | 3 | 2 | | 1 |
| 25.Sore mouth | | 5 | 4 | | 3 | 2 | | 1 |
| 26.Nausea | | 5 | 4 | | 3 | 2 | | 1 |
| 27.Vomitting | | 5 | 4 | | 3 | 2 | | 1 |
| 28.Dry retching | | 5 | 4 | | 3 | 2 | | 1 |
| 29.Feeling restless | | 5 | 4 | | 3 | 2 | | 1 |
| 30.Shaking or twitching | | 5 | 4 | | 3 | 2 | | 1 |
| 31.Shivering | | 5 | 4 | | 3 | 2 | | 1 |
| 32.Feeling too cold | | 5 | 4 | | 3 | 2 | | 1 |
| 33.Feeling dizzy | | 5 | 4 | | 3 | 2 | | 1 |
| 34. Feeling confused | | 5 | 4 | | 3 | 2 | | 1 |
| 35.Difficulty falling asleep | | 5 | 4 | | 3 | 2 | | 1 |
| 36.Bad dreams | | 5 | 4 | | 3 | 2 | | 1 |
| 37.Feeling angry | | 5 | 4 | | 3 | 2 | | 1 |
| 38.Feeling anxious | | 5 | 4 | | 3 | 2 | | 1 |
| 39.Feeling depressed | | 5 | 4 | | 3 | 2 | | 1 |
| 40.Feeling alone | | 5 | 4 | | 3 | 2 | | 1 |

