**Randomization and blinding**

This study is an observer-blinded, randomized control trial. Randomization, stratified by surgeons, will be performed by independent personnel ([name]), through two random digit tables generated by computer software. The random digit and the information of group allocation for every enrolled patient is sealed with an opaque envelope. Two anesthesiologists ([name], [name]) will perform all the intraoperative assessments, and two other anesthesiologists ([name], [name]) will perform all the postoperative assessments; two surgeons ([name], [name]) will assess if the patients achieve the standard of hospital discharge, and two independent persons ([name], [name]) will perform the statistical analysis of the data. All these investigators are blinded to the group allocation. All procedures of TAP blockades and intubation or insertion of LMAs will be performed by the same anesthesiologist ([name]), who knows the group allocation. The flow diagram for this trial is summarized in **Figure 1**.

Identify patients with primary liver cancer

scheduled for open hepatectomy with ERAS programs

Review pre-operative assessment to determine eligibility

Obtaine informed consent

Perform randomization

(n=48)

Experimental group (TAP+LMA group):

a subcostal TAP block combined with LMA anesthesia

Control group:

general anesthesia with endotracheal intubation

Study end-points:

postoperative time of readiness for discharge; postoperative pain intensity;

time to first flatus; quality of recovery; complications; overall medical cost

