**Statistical analysis and sample size**

Statistical analyses will be performed with SPSS software version 19.0 (IBM Corporation, Armonk, NY, USA). Continuous variables are expressed as mean ± standard deviation and tested if they are normally distributed. Variables with normal distribution are compared between groups using a 2-sample Student’s *t*-test. Data without normal distribution are analyzed using non-parametric test. Blood glucose, lactate, the NRS pain score and the QoR-40 score will be compared between groups using repeated-measures analysis of variance (ANOVA). Categorical data is expressed as ratio or frequency and analyzed using Chi-square test or Fisher’s exact test. Two-tailed *P*<0.05 indicates statistical significance.

Based on our preliminary experiment consisting of 24 patients, the sample size for this trial is calculated using SAS software version 9.4 (SAS Institute Inc., Iowa City, IA, USA). The postoperative time of readiness for hospital discharge in the control group was (9 ± 2.5) days, while that of the TAP+LMA group was (7.5 ± 2.0) days. Accordingly, 42 patients are required per group to achieve 85% statistical power (1-β) at a significance level (α) of 0.05. To account for a 15% drop-out rate, we will enrolled 48 patients per group finally.

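### The last QoR-40 is timed by recovery itself, yet it enters the between-group ANOVA as an ordinary occasion, which damps the group effect

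*Protocol*

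**What the plan says.** In the Protocol, Study end-points, the QoR-40 "survey is performed before surgery, at 1 and 3 days after surgery, and on the day of discharge". Three of these four occasions have a fixed place in time; the fourth does not.

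The same section states: "The primary end-point of the study is postoperative time of readiness for hospital discharge". It gives one list of criteria for both arms, beginning "pain score less than 4, solid diet without infusion, normal bowel movement, well-healed wound, normal organ function" and continuing with white cell count, absence of fever and independence. Under Randomization and blinding, two surgeons "will assess if the patients achieve the standard of hospital discharge".

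Under Statistical analysis and sample size, "the NRS pain score and the QoR-40 score will be compared between groups using repeated-measures analysis of variance (ANOVA"). No QoR-40 occasion is left out, and the ANOVA term that serves as the test is not named.

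Quality of recovery appears among the study end-points in the flow diagram, but QoR-40 is not among the secondary end-points listed in the text.

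**The concern.** The fourth QoR-40 has no common postoperative day. Its date is driven by the outcome that the trial is meant to change. An arm that recovers more slowly gets more days before it is scored, and both arms are scored at about the same threshold.

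The questionnaire's recall window is short ("How have you been feeling in the last 24 hours"), and several items follow the discharge criteria: pain, enjoying food, washing, looking after one's appearance, usual activities. A real benefit would therefore show mainly as an earlier date, which the primary end-point already captures, and less as a higher score on that date. The ANOVA nevertheless gives this visit the same standing as days 1 and 3, and no QoR-40 is fixed after day 3.

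At stake is a report of no difference in quality of recovery that arises partly from when the last questionnaire was given.

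**Working it through.** **The plan's own figure.** The Protocol gives 9 ± 2.5 v 7.5 ± 2.0 days and 42 per group for 85% power at two-sided 0.05. The pooled SD is √((2.5² + 2.0²)/2) = 2.264. The noncentral t calculation at 42 per group gives 85.1%, so the figure reproduces. It concerns the primary end-point only; no figure is given for QoR-40.

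**Timing of the fourth occasion.** 9 − 7.5 = 1.5 days later in control on average, if discharge follows readiness.

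**Inputs for QoR-40.** From the Protocol: four occasions, 42 per group, two-sided 0.05. Assumed, because the Protocol gives nothing: a difference d = 0.4 SD on days 1 and 3, none before surgery, equal SDs, and equal correlation r between occasions of 0.3, 0.5 or 0.7. The discharge difference is taken first as zero, then as half and as all of d.

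**Formulas (SD units).**
- Group main effect over k occasions: a t-test on each patient's mean, with variance v = (1 + (k−1)r)/k.
- With the preoperative score as covariate, mean of k postoperative occasions: v = (1 + (k−1)r)/k − r².
- Noncentrality = mean difference / √(2v/42).
- Interaction: noncentral F with λ = (42/2) × Σ(difference − mean difference)² / (1 − r).

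**Worked case, r = 0.5, no difference at discharge.**
- ANOVA, four occasions: difference (0 + 0.4 + 0.4 + 0)/4 = 0.200, v = 0.625, noncentrality 0.200/0.1725 = 1.16, power 21%.
- ANOVA, discharge removed: 0.8/3 = 0.267, v = 0.667, noncentrality 0.267/0.1782 = 1.50, power 32%.
- Covariate, three postoperative occasions: 0.267, v = 0.417, noncentrality 0.267/0.1409 = 1.89, power 46%.
- Covariate, days 1 and 3: 0.400, v = 0.500, noncentrality 0.400/0.1543 = 2.59, power 73%.

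**Power by correlation.**

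| Analysis | Discharge difference | r = 0.3 | r = 0.5 | r = 0.7 |
|---|---|---|---|---|
| ANOVA main effect, four occasions | 0 | 26% | 21% | 18% |
| same | d/2 | 38% | 30% | 25% |
| ANOVA main effect, discharge removed | not used | 38% | 32% | 27% |
| Days 1 and 3, no covariate | not used | 61% | 55% | 50% |
| Covariate, discharge kept | 0 | 44% | 46% | 58% |
| same | d/2 | 62% | 65% | 77% |
| same | d | 78% | 80% | 90% |
| Covariate, days 1 and 3 | not used | 68% | 73% | 86% |
| Interaction, four occasions | 0 | 42% | 56% | 80% |
| Interaction, discharge removed | not used | 34% | 45% | 68% |

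With no difference at discharge, the main effect estimates 0.50d with four occasions and 0.67d without discharge. The preoperative score causes the rest of the dilution.

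**The case against.** **Content of the questionnaire.** A reader might infer that a discharge-day QoR-40 cannot show any difference. The documents do not support that. Many items lie outside the discharge criteria: sleep, dizziness, mood, support, and "24.Sore throat", which could plausibly differ between a tube and a laryngeal mask. The criteria set floors, such as a pain score below 4, and not equal scores. This objection stands: the difference is damped, and zero is the extreme case. With half the difference left, the discharge visit costs the main effect only about 0 to 2 points, and the baseline-adjusted analysis 6 to 8.

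**Which ANOVA term.** The Protocol does not name it, and that detail may properly sit in an analysis plan. When scores converge at discharge, the interaction gains from keeping the visit (56% v 45% at r = 0.5). This also stands, so the loss cannot be claimed for the ANOVA in general. But the interaction asks whether the profiles differ in shape, not whether recovery is better, and part of its signal would be the convergence itself.

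**Attribution.** A reader might set 21% against 73% and blame the discharge visit for the whole gap. That comparison also takes the preoperative score out of the mean and adds a covariate. Removing discharge alone moves 21% to 32%.

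**Readiness and discharge.** That patients leave only once the criteria are met is the natural reading, but the Protocol does not say so.

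**Importance.** QoR-40 is not a listed secondary end-point, and the primary analysis and sample size are untouched. That limits the weight of the point but does not remove it.

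**Conclusion.** The point holds in a limited form. A QoR-40 occasion whose date is set by recovery to a common standard is analysed as if it were a fixed time, and this pulls the group main effect toward zero.

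If no difference remains at discharge, the visit costs about 10 to 12 points of main-effect power, or about 24 to 27 points in a baseline-adjusted analysis. The cost shrinks as more of the difference persists, and it reverses if all of it does. These figures rest on an assumed 0.4 SD effect, equal correlations of 0.3 to 0.7, complete data on 42 per group, and discharge following readiness. They show the direction and rough scale and are not estimates for this trial.

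It is worth correcting before analysis. It does not threaten the primary result.

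**What to change.** In Statistical analysis and sample size, state that the between-group QoR-40 test uses postoperative days 1 and 3, with the preoperative score as covariate. State that the discharge-day score will be reported descriptively by arm, together with the postoperative day on which it was taken, and will not be used as evidence for or against a group difference in recovery.

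The covariate is part of the fix: days 1 and 3 without it give 61/55/50% in the table above, not 68/73/86%.

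The change takes a sentence or two and needs no new data. The cost is one fewer occasion in the test: about 5 to 10 points of power if the full difference persists to discharge (78/80/90% with the visit, 68/73/86% without).

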**Statistical analysis and sample size**

Statistical analyses will be performed with SPSS software version 19.0 (IBM Corporation, Armonk, NY, USA). Continuous variables are expressed as mean ± standard deviation and tested if they are normally distributed. Variables with normal distribution are compared between groups using a 2-sample Student’s *t*-test. Data without normal distribution are analyzed using non-parametric test. Blood glucose, lactate, the NRS pain score and the QoR-40 score will be compared between groups using repeated-measures analysis of variance (ANOVA). Categorical data is expressed as ratio or frequency and analyzed using Chi-square test or Fisher’s exact test. Two-tailed *P*<0.05 indicates statistical significance.

Based on our preliminary experiment consisting of 24 patients, the sample size for this trial is calculated using SAS software version 9.4 (SAS Institute Inc., Iowa City, IA, USA). The postoperative time of readiness for hospital discharge in the control group was (9 ± 2.5) days, while that of the TAP+LMA group was (7.5 ± 2.0) days. Accordingly, 42 patients are required per group to achieve 85% statistical power (1-β) at a significance level (α) of 0.05. To account for a 15% drop-out rate, we will enrolled 48 patients per group finally.

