**Patients**

Patients with primary liver cancer who is scheduled for open hepatectomy with ERAS programs (**Table 1**) will be evaluated for eligibility. Inclusion criteria are as follows: age between 18 and 65 years; body mass index of 18.5-28 kg/m^2^; number of tumor less than 3; tumor’s maximum diameter or sum of diameters smaller than 10 cm; class A or B of Child-Pugh liver function; tumor’s clinical stage as I or II; the remaining liver volume/standard liver volume ratio of >40%; no difficulty of intubation or inserting an LMA; American Society of Anesthesiologist physical status classification between I and III. Exclusion criteria are as follows: presence of comorbidities such as diabetes, pathological cardiopulmonary disease and renal insufficiency; a New York Heart Association class of heart function of III or greater; intrahepatic vascular invasion or extrahepatic metastasis of tumor seen by computerized tomography (CT) or magnetic resonance imaging (MRI); having received chemotherapy or radiotherapy before surgery; having undergone abdominal surgery; infection of the site of TAP block; allergy to any study medication; a history of alcohol or drug abuse; difficulty of communication with family or hospital staff. After randomization, patients who experience a failure of TAP block or LMA ventilation, suffer systemic poisoning from local anesthetic, are found to have extensive metastasis of tumor after laparotomy, lose blood over 1000 ml during surgery, undergo a long operating time of over 6 hours (hr), need to be transferred into intensive care unit (ICU) after surgery, or refuse to go on participating in this trial will br excluded from the analysis.

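### The primary comparison is unadjusted although plausibly prognostic liver measures are known from screening: the test is valid, but a pre-specified adjusted model could gain some precision cheaply

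*Protocol*

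**What the plan says.** Protocol, Study end-points: "The primary end-point of the study is postoperative time of readiness for hospital discharge". Fitness for discharge is judged on eight criteria. The first four concern pain, diet, bowel movement and wound; the rest are "normal organ function, normal count of white blood cell (WBC), no fever, life independence".

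Protocol, Statistical analysis and sample size: the primary end-point has no analysis of its own and falls under the general rule for continuous variables. "Variables with normal distribution are compared between groups using a 2-sample" Student's t-test; "Data without normal distribution are analyzed using non-parametric test". No covariate is mentioned. The significance rule is "Two-tailed *P*<0.05 indicates statistical significance". The sample size rests on the same unadjusted comparison: readiness "in the control group was (9 ± 2.5) days" against 7.5 ± 2.0 days with TAP+LMA, giving 42 per group for 85% power and 48 per group enrolled.

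Protocol, Patients: inclusion requires "class A or B of Child-Pugh liver function" and "the remaining liver volume/standard liver volume ratio of >40" per cent.

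Protocol, Randomization and blinding: surgeon is the only stratification factor, and it does not appear in the stated test either.

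**The concern.** Both liver measures have to be established before a patient can be randomised, so they are true baseline variables. After liver resection it is reasonable to expect that preoperative liver function and planned remnant volume help to predict when organ function is judged normal, and hence when the patient is fit to leave. Both can still vary among eligible patients: there are two Child-Pugh classes, and the ratio has a lower limit only. Randomisation does not balance either of them by design.

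If they are prognostic, a model that includes them narrows the confidence interval of the one powered comparison without adding patients. Naming them now also rules out choosing covariates after an imbalance has been seen. What is at stake is precision, not validity.

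**Working it through.** **Inputs.** From Statistical analysis and sample size: difference 9 − 7.5 = 1.5 days; SDs 2.5 and 2.0; two-sided α 0.05; 42 per group. The joint R² of the two liver covariates is not in the protocol and is assumed over a range.

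**Step 1: the protocol's own figure.**
- Pooled SD = √((2.5² + 2.0²)/2) = √5.125 = 2.264.
- SE = 2.264 × √(2/42) = 0.494.
- Non-centrality = 1.5/0.494 = 3.036; 82 df; critical t = 1.989.
- Power from the noncentral t = 85.1%. At 41 per group it is 84.2%, so 42 is the smallest number that reaches 85%. The stated figure is reproduced.

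**Step 2: adjustment for the two liver covariates (k = 2).**
- Residual SD = 2.264 × √(1 − R²).
- The SE is inflated for estimating the covariate effects by √(1 + k/(2n − k − 3)) = √(1 + 2/79) = 1.0126.
- df = 84 − 2 − 2 = 80; critical t = 1.990.

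| Assumed R² | SE (days) | Non-centrality | Power, 42 per group |
|---|---|---|---|
| 0 | 0.500 | 2.999 | 84.2% |
| 0.025 | 0.494 | 3.037 | 85.1% (break-even) |
| 0.05 | 0.488 | 3.077 | 86.0% |
| 0.10 | 0.475 | 3.161 | 87.8% |
| 0.20 | 0.447 | 3.353 | 91.2% |

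Without the inflation factor, and charging only the two degrees of freedom, R² 0 gives 85.1% and R² 0.10 gives 88.5%. The table is the more cautious calculation.

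**Step 3: fewer evaluable patients.** The protocol's 15% drop-out applied to 48 leaves 48 × 0.85 = 40.8 per group. At 40 per group the unadjusted power is 83.3%; adjusted, it is 82.3%, 84.2%, 86.1% and 89.8% at R² 0, 0.05, 0.10 and 0.20. An R² of about 0.07 brings it back to about 85%.

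**Step 4: what these R² values would require.** For a two-class covariate, R² = p(1 − p)δ²/5.125, where p is the share of Child-Pugh B patients and δ their extra days. Neither is given; p is assumed to be 10% or 20%. For Child-Pugh class alone:
- R² 0.025: δ = √(0.025 × 5.125/0.09) = 1.2 days at p = 10%; 0.9 days at 20%.
- R² 0.10: δ = 2.4 days at 10%; 1.8 days at 20%.
- R² 0.20: δ = 3.4 days at 10%; 2.5 days at 20%.

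The planned treatment effect is 1.5 days. Break-even therefore needs a modest effect of class, and the upper rows of the table need a large one unless the volume ratio contributes as well.

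**Step 5: surgeon.** Surgeon costs one degree of freedom for each surgeon beyond the first. If there are two (assumed), and surgeon is counted as a third covariate that explains nothing, power at a liver R² of 0 is 83.7%. This is pessimistic, because stratification already balances surgeon between the arms.

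**The case against.** The strongest reply is that nothing is wrong. The t-test is valid under randomisation and delivers its planned power at 42 per group; the sample size was built on unadjusted SDs for an unadjusted test. A covariate set is often left to the SAP, which is not shown. The first part stands in full. The second stands only in part: the protocol does not leave the method open but states a test that governs the primary end-point, and improving a stated choice is a fair comment.

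Four stronger readings are tempting, and the documents do not support them.

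- **A reader might infer that planned power is being lost.** It is not; 85.1% is what the stated test gives. Any gain rests on an R² that the protocol does not supply, and adjustment costs about 1 point if that R² is zero. The eligibility limits (Child-Pugh A or B, ratio above 40%, restricted tumour burden, no major comorbidity) may narrow the prognostic spread and weaken the correlations.
- **A reader might infer that the two covariates act directly on the discharge criteria.** Organ function is one criterion of eight and does not name the liver; none mentions remnant volume. The link is plausible, not documented.
- **A reader might infer that the values are already in the trial data.** That follows only from screening. The variables listed as recorded under Study end-points include neither, and checking a ratio against 40% need not leave a stored continuous value.
- **A reader might infer that a chance imbalance would bias the result.** Across randomisations it does not; the unadjusted test and its interval already allow for it. Adjustment removes part of that variation in the trial at hand.

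**Conclusion.** The point holds as a low-severity improvement. The protocol fixes an unadjusted comparison for its primary end-point while two plausibly prognostic baseline measures are known for every randomised patient and the stratification factor goes unused. The stated test and the 42 per group are correct as they stand.

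At 42 per group the effect of adjusting for the two liver measures runs from a loss of about 1 point (85.1% to 84.2%) at R² 0, through no change near 0.025, to gains of about 1, 3 and 6 points at 0.05, 0.10 and 0.20. These figures assume the protocol's means and SDs, a linear model with common residual variance, and covariates that together use two degrees of freedom. The documents cannot say where in the range the trial lies. The case for the change is that its possible cost is small and known, while its possible gain is larger.

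**What to change.** Name one primary analysis for this end-point: a linear model of days to readiness with treatment, surgeon, Child-Pugh class (A/B) and the remnant-to-standard liver volume ratio (continuous), all fixed before any outcome data are seen. Report the adjusted difference in days with its 95% confidence interval. Keep the unadjusted comparison as a sensitivity analysis. Add the Child-Pugh class and the numerical volume ratio from screening to the case report form.

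The cost is a change of wording and two data fields, with no extra patients or procedures for values that screening already has to establish. The statistical cost is about 1 point of power if the liver covariates prove unrelated to outcome, plus the degrees of freedom used for surgeon. The sample size need not change.
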